### Inclusion criteria

Primary knee OA defined according to ACR classification criteria (knee pain plus 3 of: age > 50 years, morning stiffness lasting < 30 minutes, crepitus, bony tenderness, no palpable warmth) [27].Pain severity of ≥ 20 points on the Western Ontario and McMaster Universities (WOMAC) numerical rating scale (range 0 to 50 points) at the study knee [28].Stable analgesic regime for 2 months before entering the study.

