### Screening assessment

A screening assessment will be conducted by the research nurse to ensure potential participants meet the inclusion and exclusion criteria. Potential participants’ GPs will be asked to confirm whether there any contraindications to the use of nortriptyline.

The study Clinical Review Team will decide each potential participant’s eligibility for the study. Once eligibility has been confirmed a baseline assessment will be undertaken. Participants will be asked to record NSAID and other analgesic use for 2 weeks before their baseline assessment.

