### Steady dose treatment period (weeks 8–14)

Following the initial dose-adjustment period, participants will continue at their maximum tolerated or effective dose for 6 weeks, a period consistent with published recommendations on OA research [32]. During this period participants will not be routinely contacted but they will be encouraged to contact the research nurse by phone if they have questions relating to their study medication.

Participants will be free to use their usual pain relieving medication as prescribed by their GP during the study period. Participants’ GPs will be informed of their patients’ participation in the study and will be asked not to prescribe nortriptyline or any other antidepressants to participants during the study period.

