### Data management and statistical analysis

Participants’ data will be recorded in individual participant record booklets. Data will be entered into an Access database (Microsoft, Redmond, WA, USA) and then exported to the latest available versions of R and Stata (StataCorp, College Station, TX, USA) [41].

Data analysis will be performed on an intention-to-treat basis with primary and secondary outcomes compared between participants randomised to nortriptyline versus those randomised to placebo regardless of adherence to entry criteria, study medication actually taken, treatment withdrawal, or protocol deviation. A per-protocol analysis will also be performed. Unit of analysis will be at the level of the patient, where patients with OA in both knees will choose the most symptomatic to be the one under study. No interim analyses will be undertaken. All statistical tests will be 2-sided and a level of significance (alpha) of ≤ 0.05 set for all confidence intervals and *p* values. Demographic characteristics and baseline data will be summarised using descriptive statistics, and presented by treatment group. The mean and standard deviation of participants’ WOMAC pain score at 14 weeks follow-up, and change between baseline and 14 weeks, will be calculated for each treatment group.

The primary outcome of the study will be the size of the treatment effect (mean difference in pain between treatment groups at 14 weeks adjusting for differences at baseline), which will be determined using linear regression modelling including treatment group as fixed effect and baseline pain scores as a covariate. A secondary analysis of this primary outcome will be conducted using multivariable linear regression, adjusting for pre-randomisation variables reasonably expected to predict a favourable outcome (duration of disease, medication use at baseline, and use of assistive devices), and participants’ use of other analgesics (paracetamol, NSAIDs, and opioids) in the 2 final weeks of the study period (weeks 12–14). Secondary continuous outcome measures (WOMAC function and stiffness, patient global assessment, and quality of life measures) will be analysed in a similar manner.

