As secondary analysis, patients will be dichotomised according to the OMERACT-OARSI set of responder criteria, defined as a high improvement in pain or function, or a moderate improvement in at least two of pain, function, or patient’s global assessment [34]. Incident rates will be calculated for this and other binary outcomes (including use of other pain medications, adverse events, and tricyclic side effects) and compared using chi-square or Fisher exact tests. Generalised linear regression models will be used to calculate absolute and relative differences in risk between treatment groups with 95 % confidence intervals, adjusting for other variables as appropriate. Self-reported treatment dosage over the past 2 weeks will be summarised for each follow-up, as will the number of participants discontinuing treatment and reasons for doing so. The incidence of all suspect serious treatment reactions will be presented in line with the CONSORT 2010 recommendations [42].

Participants who are missing outcome data will be included in the analysis using modern multiple imputation methods. To determine the robustness of results per protocol analysis will be performed, excluding participants with major protocol violations such as cross-over treatments, withdrawals and loss-to-follow-up. Dose-response will be investigated by entering final dose achieved as a predictor in regression models.

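### The only stated analysis of weeks 12–14 analgesic use is yes/no, which cannot show a participant cutting down without stopping

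*Protocol article*

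**What the plan says.** Under Secondary outcomes, the protocol article lists participant-recorded use of NSAIDs and other analgesics over the last two weeks of the study. Data management and statistical analysis classes this with "other binary outcomes (including use of other pain medications, adverse events, and tricyclic side effects) and compared using chi-square or Fisher exact tests". The next sentence adds that "Generalised linear regression models will be used to calculate absolute and relative differences in risk between treatment groups", with confidence intervals and "adjusting for other variables as appropriate". No covariate is named there.

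The same section gives baseline-adjusted linear regression to another group of outcomes: "Secondary continuous outcome measures (WOMAC function and stiffness, patient global assessment, and quality of life measures) will be analysed in a similar manner". Analgesic use is not in that list.

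Three other places bear on how the outcome will behave:

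- Inclusion criteria: "Stable analgesic regime for 2 months before entering the study".
- Screening assessment: "Participants will be asked to record NSAID and other analgesic use for 2 weeks before their baseline assessment".
- Steady dose treatment period: "Participants will be free to use their usual pain relieving medication as prescribed by their GP during the study period".

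**The concern.** This is a choice that the article states, not a detail it leaves open: the outcome is binary and the tests are those for proportions. In people with moderate to severe pain on a stable regime, who may keep taking their usual drugs, many are likely to report some use in both two-week windows. Someone who goes from a daily NSAID to one tablet a fortnight is then coded as unchanged.

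What is at stake is one secondary outcome, but a relevant one. The Background section stresses the renal, gastrointestinal and cardiovascular harms of NSAIDs, so lower exposure short of stopping would matter to patients. It would also help in reading the pain result, because background analgesia is allowed in both arms. The stated analysis could miss such a reduction.

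**Working it through.** **The plan's own figure.** The sample size is for WOMAC pain: difference 5, SD 10, two-sided alpha 0.05, power 90%. Per arm, n = 2 × (1.960 + 1.282)² × 10² / 5² = 84.1, so 85. Allowing for 15% loss, 85 / 0.85 = 100. Both stated figures reproduce. The article also says that this size suffices for the OMERACT-OARSI responder outcome. It gives no rate, effect or power for analgesic use, so every usage figure below is an assumption. All calculations use 85 per arm.

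**Closed-form check, yes/no outcome.** With difference d, mean proportion p̄ and arm proportions p₀ and p₁, power = Φ{[d√n − 1.960√(2p̄(1−p̄))] / √(p₀(1−p₀) + p₁(1−p₁))}. For 90% v 80% this is (0.922 − 0.990)/0.500 = −0.136, so 44.6%. With 60–95% users in the control arm, power is 26–59% for a 10-point fall and 10–23% for a 5-point fall.

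**Closed-form check, quantity adjusted for baseline.** With standardised difference δ and baseline correlation ρ, power = Φ{δ√(n/2)/√(1−ρ²) − 1.960}. For δ = 0.3 and ρ = 0.5 this is 0.346 × 6.519 − 1.960 = 0.298, so 62%. For ρ of 0.5–0.7, power is 62–78% at δ = 0.3 and 85–96% at δ = 0.4.

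These two checks are not matched to each other. Simulation is needed to apply one drug effect to both analyses.

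**Simulation 1: days of use out of 14.** Days are binomial(14, p), with p logit-normal (SD 2) and latent correlation 0.7, which gives an observed baseline to follow-up correlation of about 0.6. Days are analysed by regression on baseline days. Under no effect both tests reject about 5% of the time.

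| Assumed effect | Mean days, placebo v active | Any use | Chi-square | Days, baseline-adjusted |
|---|---|---|---|---|
| All cut down, 0.6 logits | 7.0 v 5.7 | – | 17% | 59% |
| All cut down, 0.9 logits | 7.0 v 5.1 | 91% v 83% | 36% | 91% |
| All cut down, heavier users | 8.7 v 6.8 | 96% v 91% | 24% | 92% |
| 15% of active arm stop | 7.0 v 5.9 | 91% v 78% | 70% | 38% |
| 20% of active arm stop | – | – | 89% | 58% |

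Repeat runs gave 19% v 62% for the first row, 37% v 92% for the second and 71% v 38% for the fourth. If only 35–52% use any analgesic, a 0.9-logit shift gives chi-square 42–50% and days 53–71%, so the gap is smaller.

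**Simulation 2: log-normal amount.** Log SD is 0.7 and log-scale baseline correlation 0.6; 5% of placebo users stop. Power is given for 60% / 80% / 95% baseline users.

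| Assumed effect | Chi-square | Any use, adjusted for baseline use | Amount, baseline-adjusted |
|---|---|---|---|
| 30% cut, no extra stopping | 5 / 5 / 5% | 6 / 5 / 4% | 66 / 77 / 87% |
| 30% cut, 10 points more stopping | 14 / 21 / 43% | 42 / 50 / 59% | 81 / 92 / 96% |
| 10% cut, 15 points more stopping | 24 / 42 / 70% | 68 / 80 / 85% | 39 / 52 / 58% |
| Stopping only, 20 points | 36 / 63 / 90% | 84 / 95 / 97% | 27 / 38 / 42% |

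The two models agree on the pattern. Amount wins when people reduce, and any use wins when they stop. Adjusting any use for baseline use helps a lot in the second model, where no baseline non-user starts an analgesic. It adds little in the first (36% to 38%, and 26% to 28% in the heavier-use setting). In neither model does it recover the information on reduction.

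**The case against.** The strongest reply has five parts.

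- **Adjustment is open.** The generalised linear models can include baseline use, and baseline medication use is a named covariate in the secondary pain model. A reader might infer that the pre-baseline record is thrown away. The article does not say so; it leaves the covariates unnamed. This stands. But those models still estimate risks of a binary outcome, so adjustment does not bring back the amount.
- **Amount may not be recorded.** The article speaks only of use, never of days, tablets or dose. Two weeks of participant recording suggests more than a single yes/no, but that is an inference. This stands, and the fix is conditional on it.
- **The loss of power depends on the assumed effect.** A reader might conclude that most of the power is lost, or that this outcome will be null whatever the drug does. Neither is supported: with 15% stopping, chi-square is the better test. A stable regime also sets no minimum use, so stable low or nil use qualifies, and prevalence within one drug class may be well below that for any analgesic.
- **Importance is limited.** The Hypotheses section covers pain and function only. A reader might infer that the pain result cannot be interpreted without an amount analysis. That goes too far: the primary comparison is of nortriptyline added to usual care, and a secondary pain model already includes weeks 12–14 analgesic use.
- **An analysis plan may add more.** An unseen plan could include an amount analysis, and the article does not exclude one. That is possible, but the analysis the article does state is binary, and analgesic use is left out of its list of continuous outcomes.

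**Conclusion.** The point holds in limited form. As stated, the analysis of weeks 12–14 analgesic use cannot detect reduction short of stopping, in a population where many may be users at both times. With 85 per arm and assumed usage patterns, chi-square power is about 17–37% against 59–92% for baseline-adjusted days when participants mainly cut down. It is about 70% against 38% in the other direction when the effect is mainly stopping. The documents give no basis for choosing between these patterns, so the case is for having both analyses, not for replacing one with the other. The result rests on the assumed distributions, a baseline correlation of about 0.6, and records that capture amount. It concerns one secondary outcome.

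**What to change.** Before unblinding, pre-specify an analysis of days or amount of analgesic use in weeks 12–14, overall and by class (paracetamol, NSAID, opioid). Adjust it for the same measure from the two-week pre-baseline record, using linear or negative-binomial regression with robust standard errors. State first whether the records capture days or amount; if they do not, this part cannot be done and the limitation should be reported.

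Keep the any-use comparison as a formal analysis and name baseline use as its covariate. Reducing it to a descriptive table would lose power if participants mainly stop.

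The cost is some extra coding of the records and one more secondary analysis to report.

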### Sample size

The minimum important clinical difference for a reduction in pain measured using the WOMAC osteoarthritis index has been determined to be about 10 % of the scale maximum, or a total difference of 5 points on the WOMAC pain numerical rating scale (range 0 to 50) [39]. A sample size of 85 per group will give at least 90 % power at a 2-sided significance level of 0.05 to detect a difference in treatment effect of 5 points between the nortriptyline and placebo groups. The sample size was calculated using a pooled standard deviation 10 points estimated from previous studies, [40] and conservatively assuming no correlation between baseline and follow-up scores. This sample size also allows for detection of the minimum important clinical difference in the proportion of participants responding to treatment according to the Outcome Measures in Rheumatology-OARSI (OMERACT-OARSI) criteria [34]. The sample size will be inflated to 100 participants per group (200 in total) to account for a possible 15 % loss-to-follow-up.

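### The responder outcome gets an unadjusted chi-square or Fisher p value beside an interval from a separate model; both should come from the planned model, adjusted for baseline

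*Protocol article*

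**What the plan says.** Three statements in the Protocol article, Data management and statistical analysis, bear on the same binary outcomes.

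- The responder outcome, use of other pain medication, adverse events and tricyclic side effects are "compared using chi-square or Fisher exact tests".
- Absolute and relative risk differences with 95% intervals come from generalised linear models, "adjusting for other variables as appropriate".
- "Participants who are missing outcome data will be included in the analysis using modern multiple imputation methods".

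The same section compares primary and secondary outcomes by intention to treat. It analyses the primary outcome, and in a similar manner the continuous secondary outcomes, by linear regression with the baseline score as a covariate.

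The outcome measures are recorded at baseline (Baseline assessment measurements). Analgesic use is recorded for 2 weeks before the baseline visit (Screening assessment).

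The Sample size section also says that the trial is large enough for the responder outcome, but gives no response rates or power for it.

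**The concern.** For one outcome, the p value and the interval are assigned to two different analyses. The test takes no covariates; the model may. The model can be fitted in each imputed data set and pooled in the standard way; the named tests cannot so easily. The two results may therefore rest on different adjustments, and possibly on different participants.

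Responder status is built from improvement in pain, function and global assessment, so it depends on baseline values that the stated test ignores. The continuous outcomes do use their baseline values. At stake are some power on the responder outcome and the awkward case of a p value on one side of 0.05 beside an interval on the other.

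**Working it through.** **1. The plan's own figures reproduce.** Inputs from Sample size: difference 5 points, "pooled standard deviation 10 points estimated from previous studies", two-sided alpha 0.05, power 90%.

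n per group = 2 × (1.960 + 1.282)² × 10² / 5² = 2 × 10.51 × 4 = 84.1, rounded up to 85. Power at 85 per group is 90.3%. Inflation: 85 / (1 − 0.15) = 100 per group. Both stated figures are right. They concern the pain score, not the responder outcome.

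**2. The two results for the responder outcome, side by side.**

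| | p value | 95% interval |
|---|---|---|
| Method | chi-square or Fisher | generalised linear model |
| Covariates | none | allowed, not named |
| Pooling over imputations | chi-square: approximate methods; Fisher: no standard rule | Rubin's rules |

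**3. Why baseline can matter.** Improvement is baseline minus follow-up. With baseline SD s_b, follow-up SD s_f and correlation ρ between the two scores,

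corr(baseline, improvement) = (s_b − ρ s_f) / √(s_b² + s_f² − 2ρ s_b s_f).

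Take s_f = 10 (the plan) and s_b = 5.7 (assumed, for a baseline score cut off at the entry limit of 20).

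- ρ = 0: 5.7 / √132.5 = 0.50
- ρ = 0.3: 2.7 / √98.3 = 0.27
- ρ = 0.5: 0.7 / √75.5 = 0.08

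The plan sizes the trial "conservatively assuming no correlation between baseline and follow-up scores". That is where baseline predicts improvement most strongly of these three cases, so adjustment helps most there and fades as ρ rises to 0.5.

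**4. Power on the WOMAC pain scale.** From the plan: 85 per arm, SD 10, 5-point effect. Assumed: a responder improves by 10 points or more in pain; baseline is truncated at 20 with mean about 28. 3,000 simulated trials per setting.

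| ρ | Chi-square | Fisher | Logistic, adjusted for baseline pain | Gain over chi-square |
|---|---|---|---|---|
| 0 | 59% | 54% | 67% | 8 |
| 0.3 | 72% | 67% | 74% | 2 |
| 0.5 | 84% | 79% | 84% | 0 |

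A repeat of 2,000 trials per setting (placebo improvement 5 points, baseline mean 28.5, SD 5.7) agreed to within a point. Chi-square and the model fell on opposite sides of 0.05 in 14%, 6% and 2% of its trials.

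Other assumptions shrink the gain. With baseline SD 8 before truncation and a placebo follow-up mean of 22, chi-square against adjusted model is 62.4 v 67.7%, 75.3 v 74.9% and 84.9 v 84.2% at ρ = 0, 0.3 and 0.5. With a responder defined instead by a pain improvement of at least 50%, it is 65.6 v 67.6%, 75.6 v 75.5% and 81.9 v 82.7%.

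**5. Power with response rates assumed directly, 40% v 60%.** Here r is the correlation between baseline and the underlying response, not ρ.

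Unadjusted, 85 per arm: z = (0.20 × √85 − 1.96 × √(2 × 0.5 × 0.5)) / √(0.24 + 0.24) = (1.844 − 1.386) / 0.693 = 0.661, so power is 74.6%.

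The complete-data columns below use 85 per arm and 3,000 simulated trials. The last three use 100 per arm, 15% missing completely at random, 20 imputations of the underlying score and 1,500 trials.

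| r | Chi-square | Fisher | Adjusted logistic | Completers' chi-square | Imputed, unadjusted | Imputed, adjusted |
|---|---|---|---|---|---|---|
| 0 | 76.6% | 71.4% | 75.5% | 76.0% | 76.6% | 76.7% |
| 0.3 | 75.5% | 70.1% | 75.3% | 74.5% | 76.5% | 78.3% |
| 0.5 | 76.2% | 71.4% | 80.6% | 74.9% | 77.2% | 81.8% |

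At r = 0.5 with missing data, the gain is 81.8 − 74.9 = 6.9 points: 77.2 − 74.9 = 2.3 from imputation and 81.8 − 77.2 = 4.6 from adjustment. Chi-square and the adjusted model disagreed at 0.05 in 1.7 to 9.5% of trials with complete data and in 3.2 to 11.3% with missing data.

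With no treatment effect, chi-square rejected in 4.6 to 5.0% of trials and Fisher in about 3%. Both are valid; Fisher is conservative.

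**6. A wider sweep.** Over three assumed responder rules and correlations from 0 to 0.7, the adjusted model was about 0 to 7 points above chi-square, Fisher about 2 to 6 points below it, and test and model disagreed in about 1 to 13% of trials. Monte Carlo error is about 1 point throughout.

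**The case against.** The strongest reply is that the remedy is already in the plan. The generalised linear model can take baseline scores, be fitted to imputed data and give a p value. Covariates and pooling are details that an article leaves to the analysis plan, which is not shown. This stands as far as it goes: unnamed covariates and pooling rules are not counted against the article. But the article does not leave the test open. It names one that takes no covariates and places the model beside it for the interval.

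Four stronger readings are tempting, and the document does not support them.

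- *The test drops the 15% expected to be lost.* The text does not restrict the tests to completers. It promises imputation and intention to treat, and chi-square can be pooled approximately.
- *Power is certainly lost.* The gain from adjustment can be zero. It depends on a correlation and a response rule for which the article gives no expected values; zero correlation is described there as conservative, not as expected.
- *Fisher's cost falls on the responder outcome.* The plan says chi-square or Fisher. With about 85 per arm and mid-range response rates, chi-square is the natural choice.
- *All binary outcomes are affected.* Adverse events and tricyclic side effects may have no matching baseline value.

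**Conclusion.** The point holds as a minor one of consistency and efficiency. The stated test for the responder outcome is valid but ignores baseline scores in hand, fits imputation poorly, and can contradict its own interval in about 1 to 14% of simulated trials. Taking the p value from the adjusted model gains about 0 to 8 points of power over chi-square, with no loss beyond simulation error.

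These sizes rest on assumed response rules, response rates, baseline distributions and correlations, and on data missing completely at random where missing data were simulated. The response rules used are simpler than the composite OMERACT-OARSI definition.

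A reader might infer that the responder result would be invalid or the trial too small for it. Neither follows: the type I error is controlled, and the article gives no response rates against which its claim of adequate size could be tested. The outcome is secondary. The primary analysis is already adjusted for baseline and is unaffected.

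**What to change.** For the responder outcome, and for analgesic use where a matching baseline value exists:

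- Take both the p value and the 95% interval from the planned generalised linear model, and state whether the risk difference or the risk ratio carries the p value.
- Adjust for the matching baseline values: pain, function and global score for the responder outcome; baseline use for analgesics.
- Impute the components (pain, function, global assessment), derive responder status in each imputed data set, fit the model in each, and pool by Rubin's rules.

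Keep chi-square or Fisher for adverse events and tricyclic side effects.

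The cost is a sentence or two of wording and a little more programming. No new data and no change in sample size are needed, because the model and the imputation are already planned.

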### Antidepressants as a novel pain treatment in OA

The discovery of central pain-processing activity in OA has suggested a potential new therapeutic approach for pain control in OA [16]. Recent trials of the serotonin and noradrenalin reuptake inhibitors (SNRIs) venlafaxine [17] and duloxetine [18–20] have shown statistically and clinically significant reductions in pain in patients with OA. The study of venlafaxine, however, was very small (*n* = 18) and used a single-blind, placebo run-in design rather than a randomised controlled trial (RCT). The duloxetine studies were larger (*n* = 256 to *n* = 524), were double-blind RCTs, and demonstrated significantly greater reduction in pain and greater improvement in physical functioning with duloxetine than with placebo; however, duloxetine was also associated with significantly more side effects and higher rates of discontinuation than placebo. Furthermore, whilst duloxetine is licensed in New Zealand, it is not subsidised so is not readily available to many of our patients.

Tricyclic antidepressants (TCAs), which are pharmacologically-related to the SNRIs, are commonly used in other chronic pain conditions: for example, in back pain and fibromyalgia, [21–23] but their potential benefits in treating OA pain have not yet been tested in a well-designed RCT. A very small (*n* = 24) cross-over study of imipramine in 1969 suggested a reduction in OA pain [24]. However, this study had several limitations in addition to its small size: the study population was mixed and only 7 participants had OA (other participants had rheumatoid arthritis and ankylosing spondylitis), the treatment periods were short (3 weeks), and there was no washout period between treatment periods. Furthermore, imipramine has a high rate of adverse effects [25]. Nortriptyline is a better-tolerated TCA and is readily available at low cost. TCAs have a range of adverse effects, particularly dry mouth, constipation and drowsiness but nortriptyline is amongst the best tolerated [25, 26]. If nortriptyline proves to have a useful analgesic effect and a tolerable side effect burden it will be a valuable addition to the analgesic options for patients with OA.

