### Final assessment

The research nurse will assess each participant at the study clinic at week 14. The following data will be recorded:Pain using the WOMAC pain scalePhysical function using the WOMAC function scaleParticipant-rated global assessment using a VASQuality of life using the SF36 surveyNSAID and other analgesic use in the previous 2 weeksTricyclic adverse effects using the Antidepressant Side-Effect ChecklistOther adverse eventsParticipant’s belief about treatment arm allocation

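### Robustness is assigned to a per-protocol analysis that drops withdrawals and losses to follow-up; it can be biased and cannot probe how missing week-14 pain scores are handled

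*Protocol article*

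**What the plan says.** All of this is in the protocol article, Data management and statistical analysis, unless another section is named.

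- Main analysis: "Data analysis will be performed on an intention-to-treat basis with primary and secondary outcomes compared between participants randomised to nortriptyline versus those randomised to placebo". The same sentence says this holds whatever drug was actually taken and whether or not treatment was stopped.
- Primary model: "linear regression modelling including treatment group as fixed effect and baseline pain scores as a covariate".
- Missing data: "Participants who are missing outcome data will be included in the analysis using modern multiple imputation methods". No missingness mechanism or imputation model is given.
- Robustness, in the very next sentence: "To determine the robustness of results per protocol analysis will be performed", and this is done by "excluding participants with major protocol violations such as cross-over treatments, withdrawals and loss-to-follow-up". No other analysis is given this task. The covariate-adjusted and dose-response models are separate and do not vary the handling of missing scores.
- Final assessment: "The research nurse will assess each participant at the study clinic at week 14".
- Antidepressants as a novel pain treatment in OA, on a pharmacologically related drug: "duloxetine was also associated with significantly more side effects and higher rates of discontinuation than placebo".

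**The concern.** Two different groups are removed from the per-protocol set under one label.

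The first group stopped treatment or left. Side effects or poor relief can cause either, so the group may differ in size and prognosis between arms. Removing it breaks the randomised comparison. Nor is it obviously a violation: the intention-to-treat sentence lists treatment withdrawal and protocol deviation as separate things, while the per-protocol sentence makes withdrawal an example of a violation.

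The second group has no week-14 score. The main result depends on what is assumed about these people. Leaving them out adds no information about what they would have scored.

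The risk is one of interpretation. A per-protocol estimate close to the imputed one could be reported as confirming the primary result, although for missing scores both rest on nearly the same assumption.

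**Working it through.** **1. The plan's own figures.** Inputs from Sample size: difference 5, SD 10, two-sided alpha 0.05, 90% power.

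- n = 2 × (1.960 + 1.282)² × 10² / 5² = 84.06, so 85 per group. Power at 85 is 0.903 (normal approximation) or 0.900 (noncentral t).
- 85 / 0.85 = 100 per group, "to account for a possible 15 % loss-to-follow-up".

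These reproduce. About 15 of 100 per arm are expected to be lost. The article does not split this by arm.

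**2. Bias of the per-protocol comparison.** Let pA and pP be the fractions excluded on nortriptyline and placebo, and d the number of points by which excluded participants are worse than retained ones, taken as equal in both arms. Each full-arm mean exceeds its retained mean by p × d, so the per-protocol difference is off by −(pA − pP) × d. Negative values favour nortriptyline.

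- Assumed 20% v 10%, d = 5: 0.10 × 5 = 0.5 point.
- Assumed 20% v 10%, d = 10: 0.10 × 10 = 1.0 point.
- Equal rates and equal d: zero.

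Against the 5-point target, 0.5 to 1.0 is 10 to 20%.

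**3. Does exclusion test the imputation?** Simulation of 600 trials, 100 per arm, no true effect. There were 20 imputations from arm and baseline, compared with the primary model fitted after excluding everyone with a missing score. The missingness models are assumptions.

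| Missingness depends on | Missing, active / placebo | Full data | Imputation | Exclusion |
|---|---|---|---|---|
| baseline pain only | 19% / 8% | +0.02 | +0.02 | +0.01 |
| unseen week-14 pain | 20% / 9% | +0.05 | −0.68 | −0.68 |

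The two methods differed within a trial by about 0.10 point on average in both rows. They agree when the assumption is true, and they agree, with the same bias, when it is false. The simulation contains no participant who stopped the drug and still has a score, so it describes missing scores only.

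**4. Participants who stop but attend.** Suppose 20% of nortriptyline participants stop, attend week 14 and are at placebo-level pain, with placebo stoppers no different from other placebo participants (assumptions). Intention-to-treat gives 5 × 0.80 = 4.0 and per-protocol gives 5.0. Here the analyses differ by a full point.

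**5. What a real check on missing scores could show.** If nortriptyline participants with missing scores are at placebo-level pain (assumption), the effect in all randomised participants is 5 × (1 − m), while imputation within arm returns 5.

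- m = 15%: 4.25, overstated by 0.75.
- m = 20%: 4.00, overstated by 1.0.

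More generally, making imputed nortriptyline scores worse by delta shifts the difference by m × delta. At 15% missing, delta of 2.5, 5 or 10 gives 0.375, 0.75 or 1.5.

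**6. Scale.** With 85 observed per arm, SE = 10 × √(2/85) = 1.53. Then 0.75 / 1.53 = 0.49 and 1.0 / 1.53 = 0.65. Significance needs about 1.96 × 1.53 = 3.0 points. With the SE held fixed, full reversion would overturn estimates from 3.0 up to 3.0 / 0.85 = 3.5 (15% missing) or 3.0 / 0.80 = 3.8 (20% missing). It would not overturn an estimate of 5.

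**The case against.** The strongest reply is that stopping treatment is not the same as having a missing outcome. The intention-to-treat rule keeps people who stop, and the Final assessment section has every participant seen at week 14. A withdrawn participant who attends therefore counts with an observed score in the main analysis and is absent from the per-protocol set. This stands. A reader might infer that both analyses give all dropouts the outcomes of those who stayed, so that comparing them is empty. The documents support that only for participants with no week-14 score.

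Other points also stand, wholly or in part:

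- Missing at random is the usual default for multiple imputation but is not stated. The fortnightly telephone reviews to week 8 could inform the imputation model. The article neither says so nor rules it out.
- The article speaks of the robustness of results in general and does not claim to test the imputation. Even so, this is the only analysis given that role, and it directly follows the imputation sentence.
- An analysis plan that is not shown may add sensitivity analyses, so their absence is not the finding. The finding is that the method the article does name is poorly chosen.
- A reader might infer that the primary estimate is itself biased by the per-protocol exclusions, or that tolerators are being compared with virtually everyone on placebo. Neither follows. The exclusions leave the intention-to-treat estimate untouched, and the illustrative split retains 80% v 90%.
- The discontinuation evidence concerns duloxetine. The article describes nortriptyline as well tolerated for its class, and it undertakes to report discontinuations with reasons.

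**Conclusion.** The point holds in this limited form. The article names as its robustness check an analysis that excludes on post-randomisation events treatment may influence, and labels those events violations. That secondary estimate can be biased: 0.5 to 1.0 point under an assumed 20% v 10% split and a 5 to 10 point deficit, and nothing if the arms are alike. For participants without a week-14 score, its agreement with the imputed result is not evidence that the primary result is robust to missing data. For those who stopped but attended, a difference between the two analyses does carry information.

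The exposure of the primary result is moderate: 0.75 to 1.0 point on a 5-point effect if every nortriptyline participant with a missing score is at placebo level. That is an assumed scenario, not a forecast. It would matter for a borderline estimate and would not undo a full 5-point effect. The wording should be changed; the sample size and the primary model are unaffected.

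**What to change.** Replace the robustness sentence with three statements.

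1. Robustness of the primary intention-to-treat result will be assessed in all randomised participants by one or both of: (a) delta-adjusted imputation, adding 0 to 10 points to imputed nortriptyline week-14 pain scores and reporting the delta, if any, at which the conclusion changes; (b) reference-based imputation, drawing missing nortriptyline scores from the placebo arm.
2. The per-protocol analysis is supplementary and will not be cited as evidence of robustness to missing data.
3. Withdrawal and loss to follow-up are not protocol violations. They will be reported by arm, separating participants with a week-14 score from those without.

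Settle this before unblinding, so that the choice cannot follow the results. The cost is a change of wording and a few hours of programming in R or Stata, both already named in the article. It needs no extra participants or data. The sensitivity estimates may be less favourable to nortriptyline.
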